#### Secondary outcomes

Study personnel will follow patients (1 h into recovery room stay, PODs 1–3) and ensure the following secondary outcomes are collected, including from the patient’s medical record and pain diary: oral morphine-equivalent opioid consumption; NRS pain scores at rest and movement (taken once in recovery and twice a day [morning and evening] on PODs 1–3); and time to recovery room and hospital discharge. Pain intensity ratings on movement will be assessed by asking the patient to abduct their arm 90° on the ipsilateral side of surgery.

One of the secondary outcomes includes persistent pain at 12 months, which will be assessed using the same criteria as the primary outcome but at 12 months. Moderate-to-severe persistent pain is a binary outcome measured at 3 and 12 months defined as persistent pain with an NRS pain score of ≥ 4 at rest 24 hours before evaluation. Similarly, persistent neuropathic pain is a binary outcome defined as persistent pain at 3 or 12 months that involves neuropathic pain as indicated by the DN4 interview, a validated instrument to detect neuropathic pain [52]. The original DN4 questionnaire required a patient examination but the DN4-interview only requires self-reported data. Patients who meet the criteria for persistent pain at 3 or 12 months after surgery report on the sensory and affective qualities of their pain using the SF-MPQ-2, a reliable tool to evaluate pain in those with chronic pain. It has been validated in a breast cancer population and has been used in several analgesic trials after breast cancer surgery [53–56].

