Additionally, all patients will be asked about their emotional and physical functioning, and their quality of life at the 3- and 12-month follow-up. Emotional functioning will be evaluated using the POMS, which is a reliable instrument, validated in a breast cancer population to evaluate aspects of psychological distress (e.g., depression, anxiety, anger) [57]. Physical functioning will be measured by the interference scale of the BPI, which provides a reliable and valid assessment of interference of pain on level of functioning and has been used in a variety of post-mastectomy pain trials [58–60] and in patients with breast cancer pain [61–64]. Given the well-established inverse relationship between pain and quality of life [65, 66], we will use the EQ-5D-5L [67], which is a widely used measurement tool for assessing health-related quality of life [68]. This instrument is also commonly used in health economic evaluations, which will be explored if lidocaine infusions are shown to be significant for the primary outcome.

Cancer recurrence will be assessed at 3 and 12 months. If cancer recurrence is suspected during follow-up, RAs will review with their respective Site Principal Investigator (PI) and send relevant source documents to the coordinating center. If needed, this outcome will be sent for adjudication by two independent investigators blinded to the patient’s treatment allocation.

Adverse events (AE) will be monitored as a secondary safety outcome. Adverse events will be defined as “any noxious and unintended response to an Investigation Medicinal Product (IMP) related to any dose.” Given the half-life of lidocaine is approximately 90 min, screening for adverse events will be limited to the period of administration (intraoperative period), and immediate postoperative period (up to 24 h after surgery). AEs will be screened and reported by the attending anesthesiologists administering study medications intraoperatively and by RAs reviewing postoperative medical records. Serious adverse events (SAEs) will be monitored throughout the entire trial conduct.

Cost-effectiveness will be assessed if lidocaine significantly reduces persistent pain at 3 months to determine cost-savings from a patient and societal perspective if lidocaine is adopted widely into practice.

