### Recruitment and participant timeline

We will use recruitment strategies that we developed in our pilot trial and prior perioperative studies [36, 69]. We aim to approach patients through involved breast surgeon offices, as well as screening daily preoperative assessment clinic lists, operating room booking lists, incoming patient lists on surgical wards, and monitor operating room procedure lists for add-on surgeries. Study RAs will approach eligible patients to verify eligibility, either in person or remotely, and to obtain voluntary informed consent. In some cases, where it may not be possible for the prospective participant to sign the informed consent form, verbal consent will be obtained and baseline questionnaires will be provided to the patient. The expectation remains that the consent form will be signed and documented in-person prior to surgery. Patients may also sign the consent form online via REDCap and no study interventions will occur prior to written consent. Further, patients have the right to withdraw from the study at any time for any reason, without the need to justify their decision.

RAs will randomize patients through an online 24-h, interactive, web-based randomization system. Randomization will occur on the day of surgery to minimize the risk of surgery being postponed or cancelled after randomization. For logistical reasons, sites have the ability to randomize the day before to allow ample time for study drug preparation, or on a Friday for a Monday case.

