### Analysis

A statistical analysis plan (SAP) has not yet been completed and approved by the Steering Committee. In general, the analysis of results will be completed in the following manner but is subject to minor changes in the SAP. Patients will be analyzed according to their allocated treatment group (intention-to-treat analysis). No imputations will be made for missing data. The relative risk for the primary outcome of the presence of persistent pain at 3 months will be estimated (along with its 95% CI) from a log-binomial model that includes factors for treatment group and the stratification variables (study center, breast reconstruction). If the number of centers is large, a center will be represented by a random effect [78]. A similar analytical approach will be used for secondary binary outcomes. Treatment effects will also be quantified by calculating absolute differences between intervention groups. Analyses of continuous variables such as acute pain NRS scores at rest and movement, oral morphine-equivalent opioid consumption, time to hospital discharge, scores on SF-MPQ-2, POMS, BPI, and EQ-5D-5L will use linear regression (with transformations of outcomes if necessary) to estimate treatment effects and their 95% CIs, again with factors (or random effects) for stratification variables. Baseline characteristics in each group will be summarized without any comparative analyses. If more than 5% of participants are missing the primary outcome, the primary analysis will combine results across multiple imputed datasets, generated from a regression model using other available pain measurements. Analysis of adverse events will be summarized using count and proportions in each intervention group (lidocaine and placebo groups) and numerical values will be used for exploratory analysis between groups. All statistical analyses will be performed using the R statistical language.

Analysis of trial outcomes will be completed at the end of the trial. There will be no interim analysis for efficacy due to the possibility of introducing bias and over-estimating treatment effects [79–81].

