## Discussion

### Data management

Trial data will be collected and stored on the secure, web-based REDCap system. This data collection platform has been widely used for research within academia and industry around the world. To ensure data quality, training sessions will be provided to all research personnel involved in the trial. Standardized CRFs will be created in REDCap for collecting baseline outcome data, with real-time checks for validity and completeness.

All data will be centrally monitored for this study, and the central monitoring process will be in conjunction with procedures such as investigator’s training and meetings, and extensive written guidance to assure the conduct of the trial is in accordance with Good Clinical Practice (GCP) Guidelines. During the central monitoring process, the monitor will assess study files and documentation against GCP standards, regulatory requirements (e.g., investigator qualifications and documented training), standard operating procedures (SOPs), and any study-specific SOPs. The monitor will also assess protocol adherence (e.g., verify source documents), recruitment (e.g., verify informed consent), drug accountability (e.g., storage, use, return). All observations noted during the monitoring review will appear in the monitoring report and associated follow-up site communication. In the event that an issue is identified, through data or other means, then a teleconference to discuss the issues will be scheduled. If the issue cannot be resolved with the site personnel, the issue will be escalated to the PI. If the issue is not resolved or requires further investigation, then an on-site monitoring visit may be conducted.

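### The linear model for POMS, BPI interference and EQ-5D-5L adjusts for stratification variables only; adding each score's own baseline value, where collected, would gain precision at almost no cost

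*Protocol article*

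**What the plan says.** The Analysis section of the protocol article groups the continuous outcomes together, from acute pain ratings and opioid use to SF-MPQ-2, POMS, BPI and EQ-5D-5L. It states that their analysis "will use linear regression (with transformations of outcomes if necessary") and that the purpose is "to estimate treatment effects and their 95% CIs, again with factors (or random effects) for stratification variables". The word for repetition there points back to the primary model, whose only terms are treatment, center and reconstruction.

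Under Secondary outcomes, "all patients will be asked about their emotional and physical functioning, and their quality of life at the 3- and 12-month follow-up". These are the scores that could have a pre-surgery counterpart.

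Two other places show that data are taken before surgery. Recruitment and participant timeline says that "baseline questionnaires will be provided to the patient", and Data management says that "Standardized CRFs will be created in REDCap for collecting baseline outcome data". Neither names the instruments, and the schedule figure is not shown.

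The Analysis text is described as a general outline, "subject to minor changes in the SAP".

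**The concern.** For a questionnaire score measured before and after an intervention, the patient's own starting value is usually among the strongest predictors of the later value. A model with center and reconstruction alone leaves that variation in the residual. Two things follow. Confidence intervals for emotional function, pain interference and quality of life are wider than they need be. Any chance difference between the arms at baseline also stays in the observed estimate. The same applies to the QALY comparison if baseline EQ-5D-5L differs by chance between the arms.

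The article is not silent here. It states a model and a covariate set and announces only minor changes. A covariate is best added before anyone has seen outcome data by arm; added afterwards, it invites a charge of selective analysis.

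**Working it through.** **The plan's own figure.** No precision or power figure is given for any continuous outcome. The only stated size is the total of 1,602 for the primary outcome: 30% against 22.5% (25% relative reduction), 90% power, two-sided 5%, 10% loss.

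- The standard two-proportion formula gives 722 per arm, 1,444 in total. Then 1,444 / 0.9 = 1,605 after rounding up, which agrees with 1,602 to within rounding and choice of formula.
- Patients analyzed: 1,602 × 0.9 / 2 = about 721 per arm. This is used below.

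**Gain from the baseline covariate.** The article gives no baseline-to-follow-up correlation *r*, so 0.5 is assumed, with a range of 0.4 to 0.6.

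- Residual variance with the covariate, relative to without: 1 − r²
- Standard error ratio: √(1 − r²)
- Equivalent sample size: 1 / (1 − r²)
- Standardized difference detectable with 80% power: (1.960 + 0.842) × √(2/721) × √(1 − r²). Without the covariate this is 0.148.

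| r (assumed) | Variance cut | SE ratio | Equivalent patients | Detectable difference |
|---|---|---|---|---|
| 0.4 | 16% | 0.917 | 1 / 0.84 = 1.19 | 0.135 |
| 0.5 | 25% | 0.866 | 1 / 0.75 = 1.33 | 0.128 |
| 0.6 | 36% | 0.800 | 1 / 0.64 = 1.56 | 0.118 |

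The variance cut and the gain in patients are different quantities: 16% to 36% for the first, 19% to 56% for the second.

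**Which outcomes this reaches.** It reaches POMS, BPI interference and EQ-5D-5L, which are asked of all patients. It does not reach postoperative opioid use or time to discharge, which have no pre-surgery value of the same measure. Nor does it reach SF-MPQ-2, which is described only for patients who meet the persistent pain criteria. For BPI the correlation may lie below the assumed range. The Exclusion criteria remove patients with a known chronic pain disorder at the surgical site or the ipsilateral chest wall, shoulder or arm in the 3 months before surgery, so baseline interference may sit near its floor.

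**The case against.** The strongest reply is that covariates for secondary outcomes belong in the SAP, which was still pending, and that no sentence says POMS, BPI or EQ-5D-5L is given before surgery. The abbreviations list includes a Pain Catastrophizing Scale that appears nowhere else in the text shown, so the baseline questionnaires may be something else. The loss is also modest: without the covariate the trial can already detect a standardized difference of 0.148, and the intervals are valid, only wider.

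Most of this stands, and it limits the point to a conditional improvement. It does not remove it, because the article names a specific covariate set and also says that baseline outcome data are collected.

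A reader might go further and infer that the standard errors for acute pain are too small. Ratings are "taken once in recovery and twice a day [morning and evening] on PODs 1–3", which makes six per patient on those days, and the Analysis section names linear regression without a patient effect. If all six entered one model as independent rows, with an assumed within-patient correlation of 0.5, the design effect would be 1 + 5 × 0.5 = 3.5. The standard error would then be too small by a factor of √3.5 = 1.87, and a nominal 5% test would reject about 29.5% of true nulls. But the article nowhere says that the ratings are pooled in this way. Separate models per time point keep the 5% level for each test. So does a per-patient mean: in simulations with 721 per arm and six ratings it rejected 4.4% to 6.0% of true nulls. No understated error is shown, and how the repeated ratings are handled is detail for the SAP.

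A reader might also assume that a QALY regression is planned and lacks a baseline term. The article describes a cost-effectiveness ratio, net benefit and bootstrapping, run only if the primary outcome is significant, and no such regression.

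**Conclusion.** The point holds as a low-cost improvement to secondary analyses. The stated model leaves out baseline scores that may already be in the database. Under randomization this costs precision and introduces no bias.

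At the assumed correlations the loss is worth having back, but it threatens no conclusion of the trial. The size rests on two assumptions that the documents do not settle: that these instruments were among the baseline questionnaires, and that the correlation lies near 0.4 to 0.6.

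**What to change.** State in the SAP that POMS, BPI interference and EQ-5D-5L at 3 and 12 months are each analyzed with the score's own baseline value as a covariate, in addition to treatment and the stratification variables, wherever that baseline was collected. State also that QALY differences between the arms are adjusted for baseline EQ-5D-5L if it was measured. Name the baseline instruments in the same place, and say how a missing baseline value is handled, so that adding the covariate does not drop patients.

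As a suggestion only, the SAP could name the analysis of the acute pain ratings on PODs 1–3: a mixed model with a patient random effect, or a per-patient mean.

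The cost is SAP wording, settled before unblinding. It needs no new data and no change to the sample size. If a baseline score was not collected, the stated model stays as it is for that outcome.

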## Discussion

### Data management

Trial data will be collected and stored on the secure, web-based REDCap system. This data collection platform has been widely used for research within academia and industry around the world. To ensure data quality, training sessions will be provided to all research personnel involved in the trial. Standardized CRFs will be created in REDCap for collecting baseline outcome data, with real-time checks for validity and completeness.

All data will be centrally monitored for this study, and the central monitoring process will be in conjunction with procedures such as investigator’s training and meetings, and extensive written guidance to assure the conduct of the trial is in accordance with Good Clinical Practice (GCP) Guidelines. During the central monitoring process, the monitor will assess study files and documentation against GCP standards, regulatory requirements (e.g., investigator qualifications and documented training), standard operating procedures (SOPs), and any study-specific SOPs. The monitor will also assess protocol adherence (e.g., verify source documents), recruitment (e.g., verify informed consent), drug accountability (e.g., storage, use, return). All observations noted during the monitoring review will appear in the monitoring report and associated follow-up site communication. In the event that an issue is identified, through data or other means, then a teleconference to discuss the issues will be scheduled. If the issue cannot be resolved with the site personnel, the issue will be escalated to the PI. If the issue is not resolved or requires further investigation, then an on-site monitoring visit may be conducted.

### Data access and confidentiality

User privileges in the REDCap system will require active usage; otherwise, access automatically relapses after 6 months of inactivity. REDCap also implements authentication to validate the identity of end-users that log into the system. After completion of recruitment and all follow-ups, trial data will be stored on a secured online cloud-based repository for analysis on the primary and secondary outcomes. All trial data will be available to trial PIs and ACTU. The trial dataset can be made available upon request by individual recruitment sites through a data sharing agreement for proposed secondary analyses on the dataset. All secondary analyses will have to be reviewed and approved by the Steering Committee. Active maintenance of the data repository will be governed by the ACTU and Sponsor. All trial data will be de-identified and anonymized using REDCap, which generates a study identifier that cannot be linked to the participant’s name or personal information. This is done to protect identities of enrolled participants, in keeping with the Personal Health Information Protection Act.

### Independent data safety and monitoring board

An Independent Data Safety and Monitoring Board (IDSMB) has been established, composed of a methodologist, pain physician and researcher, and statistician. The IDSMB will meet after every 400 patients are recruited and at the end of the trial. They will review the unblinded safety and efficacy (if requested) data provided to them by the IDSMB-Reporting Statistician to make recommendations to the Principal Investigators and Steering Committee. The IDSMB will provide recommendations about stopping the study based on considerations of harm associated with the treatment. There are no specific stopping boundaries used but at an interim safety analysis, the IDSMB members will review serious adverse events, both expected and unexpected, to determine if there is a need to stop the trial early due to harm. In addition, the IDSMB may make observations or recommendations to the sponsor about, but not limited to, the following: definitions of and responses to adverse events and patterns in adverse events; benefit/risk ratio of procedures and participant burden; selection, recruitment, and retention of participants; adherence to protocol requirements; completeness, quality, and analysis of measurements; amendments to the study protocol and consent forms; performance of individual centers and core labs; and participant safety.

### Patient engagement

A Patient Advisory Committee (PAC) comprised of representatives from patient organizations and patients with lived experience of chronic pain will meet quarterly to discuss and provide input in the trial conduct, analysis, knowledge translation, and mobilization efforts. A member of the PAC will also sit on the trial Steering Committee to ensure that patient views, concerns, needs, and preferences are incorporated and part of all major decisions pertaining to the trial.

### Knowledge translation

Integrated Knowledge Translation (IKT) strategies will include empowering knowledge users on our investigative team (i.e., anesthesiologists, breast surgeons, pain medicine clinicians) to include trial results into their practice and disseminate to their respective institutions. As part of IKT and end-of-grant KT strategies, we will disseminate our findings to practitioners, patients, the public, and other knowledge users via publishing the results in peer-reviewed medical journals, a coordinated social media strategy involving influential online stakeholder groups, media relations with professional anesthesia and surgery associations (e.g., Canadian Anesthesiologists Society, American Society of Anesthesiologists, Canadian Breast Cancer Network, American Society of Breast Surgeons), and presentations at national and international conferences. We will also advocate for inclusion of trial results in updated clinical practice guidelines. All co-investigators and collaborators involved during the recruitment of trial patients, those involved in the design and development of trial protocol, and those involved in the analysis of results will be included as co-authors in the publication of the main trial results. There are currently no plans for making full trial results publicly available for open access.

### Consent for publication

Not applicable —no identifying images or other personal or clinical details of participants are presented here or will be presented in reports of the trial results. The participant information materials and informed consent form are attached as supplementary materials.

## Trial Status

The current operational protocol version number is 3.0 that was approved on March 25, 2024. Recruitment began on September 22, 2021. The approximate date when recruitment is expected to be completed in mid-2025.

## Abbreviations

ACTU: Anesthesia Clinical Trials Unit
AE: Adverse events
BPI: Brief Pain Inventory
CI: Confidence Interval
CRFs: Case Report Forms
DN4: Douleur Neuropathique 4
DSMB: Data Safety and Monitoring Board
EQ-5D-5L: EuroQol- 5 Dimension- 5 Level
GCP: Good Clinical Practice
ICER: Incremental cost-effectiveness ratio
IASP: International Association for the Study of Pain
IDSMB: Independent Data Safety and Monitoring Board
IKT: Integrated Knowledge Translation
IMMPACT: Initiative on Methods, Measurement, and Pain Assessment in Clinical Trials
IMP: Investigative Medicinal Product
INB: Incremental net-benefit
IV: Intravenous
KT: Knowledge translation
NRS: Numeric Rating Scale
OR: Operating room
PACU: Post-anesthesia care unit
PCS: Pain Catastrophizing Scale
PI: Principal Investigator
PMPS: Post-mastectomy pain syndrome
POD: Postoperative day
POMS: Profile of Mood States
QALY: Quality-adjusted life year
RA: Research assistant
RCT: Randomized controlled trial
RR: Relative risk
RRR: Relative risk reduction
SAE: Serious adverse event
SAP: Statistical analysis plan
SF-MPQ-2: Short Form McGill Pain Questionnaire 2
SGBA +: Sex- and Gender-Based Analysis Plus
